### Methods for additional analyses (e.g., subgroup analyses) {20b}

Not applicable. No additional analyses in this protocol.

### Methods in analysis to handle protocol non-adherence and any statistical methods to handle missing data {20c}

The primary analysis will follow the ITT principle, including all randomized participants regardless of adherence to maintain randomization benefits. Sensitivity analyses (per-protocol, as-treated, or instrumental variable methods) will assess robustness for major protocol deviations or treatment switches. Missing data will be addressed using multiple imputation or mixed-effects models under the missing-at-random assumption. Sensitivity analyses (worst-case imputation) will evaluate the impact of missing data, with explicit reporting of assumptions and comparisons between complete-case and imputed results.

### Plans to give access to the full protocol, participant level-data and statistical code {31c}

The final trial protocol (including amendments) will be made publicly available upon study completion via Chinese Clinical Trial Registry, open-access journal, or email connecting with the corresponding author. Deidentified individual participant data, the protocol, and analytic code will be shared per repository name policies. Requests require a signed Data use agreement and approved research proposal.

## Oversight and monitoring

### Composition of the coordinating center and trial steering committee {5d}

The trial will be overseen by three independent committees: (1) A Trial Steering Committee (meeting quarterly) comprising independent clinicians and statisticians to provide overall supervision; (2) An independent Endpoint Adjudication Committee to verify primary outcomes; (3) Day-to-day operations will be managed by the Coordinating Center at Beijing Friendship Hospital, responsible for participant enrollment, data collection, and protocol implementation. Rigorous safety monitoring includes: mandatory reporting of all adverse events (graded 1–3 for severity/causality) to the IRB within 48 h; quarterly independent audits of protocol/GCP compliance; and immediate notification of all stakeholders for any protocol amendments. Results will be disseminated through peer-reviewed publications and clinical trial registries, with all committees maintaining independence from the sponsor. This multi-layered oversight framework ensures both trial integrity and participant safety throughout the study duration.

### Composition of the data monitoring committee, its role and reporting structure {21a}

The independent data monitoring committee (DMC) comprises statisticians, clinical experts, and ethics representatives, unaffiliated with the sponsor and investigator team, will monitor progress and protocol adherence, review data safety and interim analyses, and report directly to the sponsor’s governance board or independent ethics committee (not the study team). Interim findings are masked to investigators unless critical safety concerns arise.

### Adverse event reporting and harms {22}

All predefined sedation-related AEs (hypoxemia, hypotension) will be recorded in CRFs with severity grading (1–3), assessed for causality (Definite/Probable/Possible), and reported to IRB within 48 h (24 h for SAEs). Any participant experiencing trial-related adverse events/harms will receive immediate medical management, free follow-up care until resolution of symptoms, referral to appropriate specialists if needed, and some compensation according to hospital Compensation Policy.

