### Concealment mechanism {16b}

The complete randomization scheme (including block sizes) will remain concealed in a restricted-access file. Emergency unblinding materials (sealed envelopes) will be attached to each participant’s CRF, accessible only to the chief anesthesiologist in case of serious adverse events.

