### Procedure for unblinding if needed {17b}

Emergency unblinding is permitted only for suspected serious adverse reactions (SAEs). The principal investigator (PI) will hold the randomization list and be responsible for unblinding if necessary. All such events will be documented within 24 h to the IRB. Sealed envelopes attached to CRFs will reveal allocation.

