## Data collection and management

### Plans for assessment and collection of outcomes {18a}

All outcomes will be systematically assessed, collected, and recorded on CRFs by blinded assessors across three phases: baseline demographics (age, sex, BMI), clinical characteristics (ASA status, STOP-Bang score, Difficulty in mask ventilation [DMV] risk factors), and room-air SpO_2_ will be collected pre-procedure; continuous vital signs (HR/SpO₂/NBP recorded every 30 s), propofol requirements, hypoxemia episodes (SpO_2_ < 90% > 10 s), procedure/recovery times, and adverse events (graded by blinded assessors) collected intraprocedure; Satisfaction (10-cm VAS), PACU recovery metrics (MOAA/S = 5 time), and AEs (graded 1–3 for severity/causality) collected post-procedure.

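### The adverse-event causality scale has no level for unlikely or unrelated and names no referent, so the rating cannot separate related from unrelated events

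*Protocol article*

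**What the plan says.** Three sections of the protocol article describe how adverse events are graded.

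- Adverse event reporting and harms {22}: "All predefined sedation-related AEs (hypoxemia, hypotension) will be recorded in CRFs with severity grading (1–3"). The same sentence has these events "assessed for causality (Definite/Probable/Possible"). The section then promises treatment, free follow-up, referral and compensation for participants with trial-related harms.
- Composition of the coordinating center {5d}: "mandatory reporting of all adverse events (graded 1–3 for severity/causality) to the IRB within 48 h".
- Plans for assessment and collection of outcomes {18a}: "AEs (graded 1–3 for severity/causality) collected post-procedure".

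Two sections describe emergency unblinding.

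- Concealment mechanism {16b}: the sealed envelopes are "accessible only to the chief anesthesiologist in case of serious adverse events".
- Procedure for unblinding {17b}: "Emergency unblinding is permitted only for suspected serious adverse reactions (SAEs"). The principal investigator holds the list and unblinds if necessary.

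**The concern.** A causality rating is useful only if an assessor can say that an event was not caused by the thing being assessed. Here every available answer is some degree of yes. An event that the assessor attributes entirely to the passage of the endoscope would still be entered as possible.

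The scale also lacks a referent. Each participant is exposed to three candidate causes at once: the blinded syringe (esketamine or saline), propofol, and the procedure. A rating of probable could mean a probable effect of any of them. Two blinded assessors with the same clinical opinion could enter different grades simply because they had different causes in mind.

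What is at stake is the information in the safety reports. The number of events rated related will equal the number graded, in both arms, by construction. The promise of care and compensation in {22} depends on an event being trial-related, and the only scale the article gives cannot mark one that is not.

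**Working it through.** No arithmetic is needed to establish the point; the check is a comparison of the sections.

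**1. Count the levels.** Section {22} names three causality levels: definite, probable and possible. Levels affirming a relationship: 3. Levels for unlikely or unrelated: 0.

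**2. Ask whether the list is an excerpt.** Sections {18a} and {5d} each give a 1 to 3 grading that covers causality as well as severity. Three grades match the three named levels, so the sections agree with each other and leave no room for a fourth, negative level.

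**3. Establish the scope.** The sentence in {22} covers predefined sedation-related events and names hypoxemia and hypotension. Section {18a} applies the grading to adverse events collected after the procedure. Section {5d} applies it to all adverse events. The statement that every graded event is affected therefore rests on {5d}, not on {22} alone.

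**4. Look for a referent.** None of the three sections says what causality is judged against. The intervention description {11a} gives propofol to everyone and adds the study syringe, so the referent cannot be inferred from exposure.

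**5. Follow the rating to its uses.** Section {5d} sends graded events to the IRB, the monitoring committee section {21a} has that committee review safety, and {22} attaches care and compensation to trial-related harms. In the first two, the rating can distinguish degrees of relatedness but not related from unrelated. In the third, it cannot exclude any event.

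**6. Check the analyses.** No method in {20a} to {20c} uses relatedness. The primary comparison is of hypoxemia incidence by arm, whatever its cause.

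**7. Compare the unblinding rules.**

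| Section | Trigger | Who acts |
|---|---|---|
| {16b} | serious adverse events, no causality condition | chief anesthesiologist |
| {17b} | suspected serious adverse reactions, abbreviated SAEs | principal investigator, if necessary |

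The triggers differ, since an adverse reaction implies suspected causation and an adverse event does not, and so do the responsible persons. Neither section refers to the causality scale.

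**The case against.** The best defence is that this is a condensed article and that the complete causality code list may sit in the full protocol or the case report form. Section {22} attaches the 1 to 3 numbering to severity and lists causality separately, so the joint wording in {18a} and {5d} could be shorthand. Section {12} has cough, hiccups, reflux/aspiration and laryngospasm recorded simply as present or absent, with no causality field. This has some force: the form is not shown, and the match between three levels and three grades is strong evidence rather than proof. But the article does not leave the scale to another document. It states one, and two other sections agree with it.

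It is also fair to say that the consequence is small. In a double-blind randomized comparison, harm is judged mainly from event incidence by arm, which the plan captures. Adverse events go to the IRB within 48 h, and serious ones within 24 h, whatever their rating, so no report is lost. This stands and limits the size of the point.

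Two stronger readings are tempting, and the documents support neither.

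- A reader might infer that, because no event can be rated unrelated, the scale makes every serious event eligible for unblinding. Section {17b} does not define suspicion by this scale and leaves the decision to the principal investigator. Section {16b} already makes the envelopes available for serious adverse events regardless of causality. Broad access comes from that section, not from the scale.
- A reader might apply the planning rates in Sample size {14} to the enrolled numbers (147 × 0.50 = 73.5 control and 147 × 0.35 = 51.45 esketamine participants with hypoxemia) and call these misclassified. They are only the planned primary-outcome counts. All of these participants also receive propofol, which the article's own background says often causes hypoxemia, so rating an episode as possibly related to sedation could be correct. The figures measure no misclassification.

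**Conclusion.** The point holds as a defect in safety reporting. As stated, the causality scale has three positive levels, no negative level and no referent. Its related-event count carries no information beyond the total number of events graded, and it cannot support the trial-related harm provision in {22}. Effects on the primary analysis, sample size and type I error: none.

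The conclusion assumes that the case report form uses the scale the article states. If the form already has an unrelated category and a named referent, what remains is a correction to the article's text. The extension beyond the predefined sedation-related events rests on {5d}.

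The discrepancy between {16b} and {17b} on unblinding is a separate inconsistency that exists whatever scale is used.

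**What to change.** 1. In {22}, add at least one negative level, such as unlikely/unrelated. One level is enough to cure the defect; separate unlikely and unrelated levels are an option.
2. State what causality is judged against: at minimum the blinded study drug. Separate ratings for propofol and the procedure would be more informative but are not essential.
3. In {18a} and {5d}, separate the severity grade (1 to 3) from the causality rating, so that the latter is no longer described as 1 to 3.
4. Say in {22} how the rating bears on the trial-related harm provision, or that the provision is decided on other grounds.
5. Reconcile {16b} and {17b} so that they give one unblinding criterion and one responsible role, and make clear whether SAE denotes an event or a reaction.

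The cost is a change to the case report form's code list and some wording, with the necessary ethics approval, and no extra visits. The downside is that the change falls during recruitment, which runs from April 2025 to December 2026. Events already graded will lack the negative option, so they should either be re-rated by blinded assessors from the existing records or be reported separately from those graded on the new scale.

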### Frequency and plans for auditing trial conduct {23}

The trial will undergo independent audits every 3 months to ensure protocol compliance and data quality. Conducted by GCP-certified auditors unaffiliated with the study team or sponsor, these audits will include: (1) unannounced on-site inspections of study procedures; (2) random verification of 10% CRFs against source documents; and (3) assessment of AE reporting completeness. Audit reports will be submitted to both the DSMB and IRB within 14 days, with corrective action plans implemented for any findings. This process maintains investigator/sponsor independence while meeting SPIRIT and GCP standards for trial oversight.

### Plans for communicating important protocol amendments to relevant parties (e.g., trial participants, ethical committees) {25}

Protocol amendments (changes to eligibility, interventions, or risks) will be submitted to ethics committees and regulatory authorities for approval before implementation. All approved protocol amendments will be promptly updated on public registries within 30 days of regulatory/ethics approval. Participants will be re-consented if changes impact trial participation.

#### Dissemination plans {31a}

Trial outcomes will be disseminated through peer-reviewed publication in an open-access journal with public results tab. No publication restrictions apply and negative/null results will be reported. Lay-summary reports will be provided to all participants upon trial completion. After publication, the full protocol will be publicly accessible on ChiCTR. Detailed data and statistical documents could be available upon reasonable request via E-mail to the corresponding author.

## Discussion

This single-center, prospective, randomized controlled trial rigorously investigates the potential of low-dose esketamine (0.25 mg/kg) to mitigate propofol-induced hypoxemia in moderate-to-high risk OSA patients undergoing painless gastroscopy. Our study design addresses critical gaps in current sedation practices for this vulnerable population (patients with moderate-to-high risk OSA) by systematically evaluating whether low-dose esketamine reduces hypoxemia incidence while maintaining hemodynamic stability during procedural sedation.

The high incidence of hypoxemia (26–85%) during propofol sedation in OSA patients arises from multifactorial pathophysiology [19–21], including anatomical airway obstruction, sedative-induced respiratory depression, chronic pharyngitis, lung compression, and procedural factors. While airway optimization remains fundamental, our focus on pharmacological adjuvants represents a novel approach to this persistent clinical challenge. The selection of esketamine is particularly promising given its unique pharmacodynamic profile that may counteract propofol’s respiratory depressive effects while maintaining adequate sedation [14, 15].

Several methodological strengths enhance the validity of our trial design. First, our use of STOP-Bang scoring (≥ 3) provides a validated, clinically practical method for OSA risk stratification [22, 23], with clear correlation to polysomnography-confirmed disease severity. Second, we have implemented objective, clinically relevant endpoints aligned with international sedation guidelines [24], including both incidence and duration metrics for hypoxemia. Third, our protocol incorporates robust safety measures, including strict gastroscopy procedure time limits (≤ 15 min) based on our previous findings [25] and comprehensive monitoring of laryngospasm as a potential indicator of esketamine’s airway protective effects.

Notably, our secondary outcomes will provide important insights into esketamine’s multidimensional effects, including the following: propofol-sparing potential and hemodynamic stability [16], reduction in involuntary movements through analgesic properties, clinician satisfaction and procedural conditions, and recovery characteristics. These assessments may help explain the mechanistic basis for any observed hypoxemia reduction while evaluating the overall clinical utility of this adjunctive approach. Our preliminary data in urologic procedures [16] and analogous studies in other contexts [26] support the biological plausibility of our hypothesis.

Potential limitations include the single-center design and focus on gastroscopy, which may affect generalizability. However, the standardized protocol and objective endpoints strengthen internal validity. Furthermore, our stratified randomization and rigorous monitoring protocols minimize confounding and ensure data quality.

This trial will provide high-quality evidence regarding esketamine’s role in improving sedation safety for OSA patients. Positive results could establish a new standard of care for this high-risk population, while negative findings would still advance our understanding of sedation pharmacology in compromised airways. Either outcome will meaningfully inform clinical practice and future research directions in procedural sedation.

## Trial status

The first participant was enrolled on April 1, 2025; the recruitment will be completed on December 31, 2026. The trial is ongoing.

## Data Availability

After the study is published, the final trial dataset will be open to the public (including the participates) through email connecting with the corresponding author.

## Abbreviations

AEs/ASA: Adverse Events/ American Society of Anesthesiologists
BMI/CRF: Body / Case Report Form
ChiCTR: Chinese Clinical Trial Registry
DBP/MAP: Diastolic Blood Pressure/ Mean Arterial Pressure
DMC/DSMB: Data Monitoring Committee/ Data and Safety Monitoring Board
ECG/SpO₂: Electrocardiogram/ Peripheral Oxygen Saturation
GCP: Good Clinical Practice
HR/RR: Heart Rate/ Respiratory Rate
IRB: Institutional Review Board
ICMJE: International Committee of Medical Journal Editors
ITT/IV: Intention-to-Treat/ Intravenous
MOAA/S: Modified Observer’s Assessment of Alertness/Sedation
NBP/SBP: Noninvasive Blood Pressure/ Systolic Blood Pressure
NMDA: N-Methyl-D-Aspartate (receptor)
OSA: Obstructive Sleep Apnea
PACU: Post-Anesthesia Care Unit
SNOSE: Sequentially Numbered, Opaque, Sealed Envelopes
STOP-Bang: Snoring, Tiredness, Observed apnea, Pressure (blood), BMI, Age, Neck size, Gender
VAS: Visual Analog Scale
